#### Population-Level Summary Measure

The mean intra-individual change score (mean delta difference) will be calculated from baseline to postintervention across the pooled cohort of 53 participants.

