#### *Pradhana Karma* (Main Procedure)

*Virechana* will be completed using *Trivrit Lehya* (drug prepared from *Operculina turperthum*) at around 7 AM.

For *paschat karma* (the postoperative procedure), after attaining hunger and when the participant ceases to feel the urge for defecation, he/she will be allowed to take a bath in warm water.

Based on the *sudhi lakshana* (signs and symptoms suggestive of a proper purgation), the participant will be advised to follow *samsarjana* (modified dietic regimen) for 1, 2, or 3 days.

The participants will be admitted to the hospital for the duration of the trial. The administered diet will be uniform for all participants. Hydration will also be monitored. Participants are restrained from doing strenuous physical activity throughout the intervention. They are also advised to sleep for a strict 6 hours to 8 hours. The strictly enforced controls on diet, hydration, physical exertion, and sleep are not external protocol restrictions but standardized, fundamental therapeutic components (*Ahara* and *Vihara*) inherent to the classical *Śodhana* (Panchakarma) and *Samsarjana Krama* (graduated postdetox dietary timeline) intervention package. These parameters are operationally deployed within an institutional setting to ensure uniform clinical delivery.

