### Statistical Measures

The change in values of the outcome measures including MDA, SOD, telomerase activity, and telomere length will be recorded. The data will be tested for normality using the Shapiro-Wilk test. They will be tested for significance using paired *t* tests (if the data are normally distributed) or the Wilcoxon Signed Rank test (if the data are not normally distributed). A *P* value <.05 will be considered significant. All statistical analysis will be conducted using SPSS version 31 (IBM Corp). Moreover, a secondary exploratory subgroup analysis will be conducted within and between the 2 cohorts (*Vamana* and *Virechana* groups) based on the distribution of the data. If the data are normally distributed, within-group analysis will be conducted using paired *t* tests and between-group analysis will be conducted with *t* tests, whereas Wilcoxon Sign Ranked tests and Mann-Whitney *U* tests will be used, respectively, for data that are not normally distributed.

Cohen *d* effect sizes will also be calculated to address the exploratory nature of the study and evaluate the clinical and biological relevance of changes in biomarkers (ie, MDA, SOD, and telomerase activity). Results will be interpreted based on the magnitude and directionality of these effect sizes (small: 0.2; medium: 0.5; large: 0.8) to provide a standardized measure of treatment impact beyond simple *P* value testing.

Given the exploratory, hypothesis-generating design of this pilot study, secondary multivariable analyses will be introduced to evaluate the influence of potential baseline confounders. For normally distributed continuous data, an analysis of covariance (ANCOVA) will compare postintervention outcomes between the 2 seasonal subcohorts (*Vamana* vs *Virechana*) using individual pre-intervention scores as the baseline covariate to mathematically adjust for initial biological variation. Additionally, to evaluate the entire cohort of 53 participants as a unified group, multiple linear regression models will be constructed using the postintervention scores as the dependent variable, entering baseline biomarker values, age, sex, and baseline BMI as independent predictors to systematically control for demographic and physical confounding variables.

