### Limitations

Placebos for procedures like *Vamana* and *Virechana* are challenging to include; therefore, this study does not include a control group. However, the resulting single-group study design raises concerns about internal validity.

In addition, this exploratory pilot trial lacks a concurrent, untreated parallel control group. Since this study operates as an investigator-initiated doctoral project embedded within a real-world clinical service, introducing an untreated healthy cohort was operationally and ethically unfeasible, as all recruited individuals are actively seeking immediate wellness interventions. To mitigate this constraint and maximize data validity, each participant serves as their own internal longitudinal control through structured pre- and postintervention paired comparisons. Furthermore, potential lifestyle and environmental confounding variables are strictly controlled by housing all 53 participants within an identical inpatient ward environment throughout the active study timeline.

We acknowledge that serum MDA and T-SOD are short-term surrogate markers of oxidative stress, not direct proof of delayed aging. In this protocol, *Śodhana* represents a complete therapeutic process including *Pūrvakarma* (internal oleation), *Pradhāna Karma* (*Vamana* or *Virechana*), and *Saṃsarjana Krama*. Therefore, acute changes in MDA and T-SOD reflect the immediate metabolic shifts of this entire multiphase cycle rather than long-term aging changes. To address this limitation, we paired these dynamic redox markers with telomerase activity. This allows us to explore whether the intense physiological “reset” caused by the complete *Śodhana* sequence correlates with any stabilizing effects on a deeper, genetic marker of cellular longevity.

The sample size calculation was also pragmatic rather than inferential. The exploratory nature of the study warrants a focus on feasibility of the protocol rather than to test the hypothesis.

The recruitment is seasonal and consecutive. Therefore, differences in environmental factors, including the climate and diet, as well as baseline biological rhythms between the 2 cohorts may act as potential modifiers for biomarker levels.

Although other biomarkers, including an interleukin panel and the microbiome, are available, we included only a limited number of biomarkers for our healthy volunteers due to financial constraints.

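### The whole-cohort regression cannot control confounding of a within-person change, as the article says it does, and it leaves out cohort

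*Protocol article*

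**What the plan says.** Under Statistical Measures, the protocol article says that "secondary multivariable analyses will be introduced to evaluate the influence of potential baseline confounders". For the cohort taken as one group, "multiple linear regression models will be constructed using the postintervention scores as the dependent variable". The article then lists the terms of the model and what they are for: "entering baseline biomarker values, age, sex, and baseline BMI as independent predictors to systematically control for demographic and physical confounding variables". No cohort or season term is listed.

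The estimand sections define the comparison as each participant's own T0 against T1 (Alternative Treatment Conditions). Population-Level Summary Measure adds: "The mean intra-individual change score (mean delta difference) will be calculated from baseline to postintervention across the pooled cohort of 53 participants". Trial Design states that each person enters one seasonal cohort only, by self-selection, so procedure and season coincide completely with cohort.

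The Limitations section concedes that "differences in environmental factors, including the climate and diet, as well as baseline biological rhythms between the 2 cohorts may act as potential modifiers". It also claims that "potential lifestyle and environmental confounding variables are strictly controlled by housing all 53 participants within an identical inpatient ward environment". Yet the Virechana section on the main procedure says that the controls on diet, hydration, exertion and sleep "are not external protocol restrictions but standardized, fundamental therapeutic components".

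**The concern.** A confounder of a pre-post contrast must differ between the two time points. Age, sex and baseline BMI do not: each person contributes the same values to both sides of their own comparison. The threats that do apply to an uncontrolled pre-post design (time trend, regression to the mean, the ward regimen, assay run) are not in the model. A report that the change held after control for demographic and physical confounders would therefore claim protection that the model cannot give.

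The one factor that splits the 53 participants by design, cohort, is missing from this model. Two procedures given in two seasons are summarised by a single regression surface, and any slope for age, sex or BMI may partly pick up a difference between cohorts.

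The housing statement has a related difficulty. If the ward rules are part of the treatment, they cannot also be confounders that the design has controlled.

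**Working it through.** **Plan's own figures.** Sample Size gives Z = 1.96, P = 0.5, margin 0.15 and 20% dropout: 1.96² × 0.25 / 0.15² = 42.68, and 42.68 / 0.80 = 53.35, stated as 53. A paired two-sided test at 0.05 with n = 53 and d = 0.395 has 80.6% power by the noncentral t distribution, against 80% stated. Both reproduce. Neither bears on the regression.

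**Does any slope carry the change?** Write post = b0 + b1·baseline + b2·age + b3·sex + b4·BMI + error. Adding a constant c to every post value raises b0 by c and leaves b1 to b4 alone. Numerically, with c = 5, the largest movement in any slope was 1.4e-14. No slope contains the mean change.

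**Does the intercept carry it?** Without centring, b0 is the prediction at baseline 0, age 0 and BMI 0. Simulation used 2,000 data sets of n = 53 split 27/26, with assumed baseline mean 10, SD 2, slope 0.6 and residual SD 1.6. The expected intercept is 10 − 0.6 × 10 = 4 plus the true change. It averaged 3.91 when the true change was 0 and 3.05 (SD 3.3) when it was −1. It is not the change.

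**What does centring give?** Least squares with an intercept passes through the sample means. With predictors centred, b0 = mean(post), so b0 − mean(baseline) = mean(post) − mean(baseline), the plain mean change. The largest discrepancy in simulation was 1e-14. This is algebra and needs no assumed values; it holds whenever both are computed on the same participants.

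Only the printed standard error moves: 0.244 unadjusted, 0.218 from the model. By hand these are √(0.4² × 2² + 1.6²)/√53 = 1.789/7.280 = 0.246 and 1.6/7.280 = 0.220. The smaller figure treats the observed covariates as fixed. Since the two estimates are identical, the mean change itself has not become more precise over repeated samples.

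**Change score or post score?** With baseline in the model, subtracting it from the outcome lowers b1 by exactly 1 and leaves the other slopes unchanged. The gain is that the centred intercept is then the mean change directly.

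**Cohort.** A centred cohort term leaves the pooled mean change as it was (largest difference 1.2e-14) and adds the between-cohort difference. With true shifts of −2 and 0, its coefficient averaged 1.99 (SD 0.46). The planned model has no term for this difference.

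**Precision.** Take two cohorts of about equal size (27 Vamana participants are reported under Results; 53 − 27 = 26 if no more enter), within-cohort SD of change 1, and means that differ by D. The pooled SD is √(1 + D²/4) and the effective-n ratio is 1/(1 + D²/4):

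| D | Pooled SD | Effective n | Loss |
|---|---|---|---|
| 0.2 | 1.005 | 0.990 | 1% |
| 0.4 | 1.020 | 0.962 | 4% |
| 0.8 | 1.077 | 0.862 | 14% |
| 1.0 | 1.118 | 0.800 | 20% |

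These rows describe the raw pooled change. In the baseline-adjusted regression, D would be counted in residual SDs.

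**The case against.** The strongest defence is that cohort is already handled. Statistical Measures plans paired tests within each cohort, t or Mann-Whitney tests between them, and an ANCOVA of the two cohorts adjusted for baseline score. That stands. A reader might infer that the plan lets two procedures pass as one effect, or that equal and opposite effects would vanish unseen in the pooled mean. The documents do not support this, because the planned cohort analyses would show it. Cohort is missing from this model, not from the plan.

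It is also fair that the mean change comes from the paired comparison, that the multivariable analyses are labelled secondary and exploratory, and that the article is silent on centring, a detail that can be left to an analysis plan. So the lack of a change parameter is not in itself the fault. The fault is the stated purpose, which fails however the predictors are coded.

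The article is candid elsewhere: it admits the lack of a control group and concern about internal validity, and Future Directions says a control arm is needed to separate the effect from caloric restriction. That tempers the risk but leaves the confounding-control sentence standing.

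On housing, an identical ward does limit variation between participants. A reader might go further and call T0 a free-living baseline. The article gives only day 0 for the first sample and says participants are admitted for the trial's duration, so that reading is an inference.

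**Conclusion.** The point holds in limited form. Under the stated estimand, the whole-cohort regression cannot control confounding by age, sex or baseline BMI, because these do not vary within a person across the contrast. Its adjusted mean change equals the unadjusted one by algebra. Omitting cohort hides heterogeneity in this model, can distort the covariate slopes and can cost precision.

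Two stronger readings should be resisted. The omission does not bias the pooled mean change. Nor is a loss of 14% to 20% of effective sample size established: it needs a cohort difference of 0.8 to 1.0 SD, the article gives no biomarker SDs or expected cohort differences, and at 0.2 to 0.4 the loss is 1% to 4%.

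The housing claim and the description of the ward rules as treatment components need reconciling. Shared housing does not separate those rules from the treatment in a pre-post contrast.

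Severity is minor to moderate: the analysis is secondary and the primary paired test is untouched.

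**What to change.** - Model the change score on baseline, age, sex, BMI and a cohort indicator, all centred at their sample means, so that the intercept is the mean change over all participants, as the estimand requires. Effect coding of cohort would instead target an equally weighted average of the two cohorts, which differs if the cohorts are unequal in size.
- Report the two cohort-specific mean changes with 95% CIs beside the pooled one. Keep the paired analysis as the source of the pooled estimate and its CI, and do not present the model's smaller standard error as a gain from adjustment.
- Describe the coefficients as predictors of change and delete the claim to control confounding. Note that the baseline slope partly reflects regression to the mean, and that the cohort coefficient cannot separate procedure from season or self-selection.
- Reword the housing sentence in Limitations: a common ward reduces variation between participants, while its diet, hydration, exertion and sleep rules belong to the package being evaluated.

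The cost is one variable already known for everyone, one degree of freedom, and wording. The article reports data analysis as still pending, so the change can be made beforehand.

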### Statistical Handling of Missing Data

This trial evaluates objective biochemical endpoints within a strictly monitored hospital inpatient setting; the incidence of missing data is anticipated to be extremely low (<5%). Any missing data points are assumed to follow a missing completely at random mechanism, as data omissions would stem strictly from random logistical or laboratory anomalies.

Missing data will be handled using an available case analysis (pairwise deletion) framework for the primary longitudinal comparisons, ensuring that all available valid pairs of pre- and postintervention biochemical metrics are fully utilized without fabricating data. To verify that this approach does not introduce statistical bias, a conservative baseline observation carried forward (BOCF) sensitivity analysis will be executed concurrently. Under the BOCF framework, any missing postintervention value will be replaced by the participant’s own baseline value, assuming zero therapeutic change. This dual-validation approach guarantees a highly transparent, noninflationary evaluation of the trial’s biochemical endpoints.

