### Participant Retention and Discontinuation Protocols

Participant retention is optimized through the fully managed inpatient environment. This trial tracks an existing clinical service where healthy volunteers are admitted as full hospital inpatients for the duration of the *Śodhana* therapy; therefore, typical outpatient compliance barriers like travel issues, appointments being forgotten, or accidental dietary deviations are naturally eliminated.

For participants who voluntarily withdraw or deviate from the intervention protocols after formal enrollment, active procedures are immediately halted to protect participant autonomy and safety. Unless written consent is completely revoked, the specific outcome data collected and retained for these individuals will consist of baseline serum MDA, T-SOD, and telomerase levels, along with a documented record of the exact chronological point and clinical reason for the protocol deviation or study exit. The reasons for nonadherence and nonretention will be recorded on the CRF. All recorded reasons will be compiled into a standardized trial flow diagram and fully disclosed in the final manuscript publication.

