### Sample Size

The sample size is feasibility-driven. It was chosen based on pragmatic constraints. As this is an exploratory study, the goal is not to achieve definitive statistical power but to establish a foundation for future, larger-scale confirmatory research. Analyzing the census of Kerala, only 30% of the population could be sampled as healthy volunteers excluding NCDs, infectious diseases, other systemic illness like cancer, and age. The sample size was calculated as 53 using the following formula;

$$n=\frac{Z_{1-\alpha /2}^{2}\times P(1-P)}{d^{2}}$$

where Z_1-α/2_=1.96 (assuming a 95% CI), *P*=.5 (expected effeciency/anticipated proportion), and d=0.15 (15% margin of error), assuming a dropout rate of 20%.

Although this sample size is rooted in regional screening feasibility, a retrospective sensitivity power analysis confirmed that a finalized cohort of 53 individuals provides 80% statistical power (*α*=.05) to detect a small-to-medium intra-individual effect size (Cohen *d*=0.395) using a 2-sided paired samples framework. This standard biostatistical validation confirmed that, although the enrollment target is grounded in regional fieldwork constraints, it remains mathematically sensitive enough to capture subtle, homeostatic optimization trends in continuous aging biomarkers (MDA, SOD, and telomerase activity) within a healthy cohort.

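### The missing-data section justifies MCAR by purely random losses of under 5%, a cause the protocol's own anticipated withdrawals contradict and a rate left unreconciled with its 20% dropout allowance

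*Protocol article*

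**What the plan says.** Four sections of the protocol article bear on this.

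- **Sample Size.** "The sample size was calculated as 53 using the following formula", with z = 1.96 ("assuming a 95% CI"), P = 0.5 ("expected effeciency/anticipated proportion") and d = 0.15 ("15% margin of error"), "assuming a dropout rate of 20" percent. The section adds that "a finalized cohort of 53 individuals provides 80% statistical power" at a two-sided alpha of 0.05 for Cohen d = 0.395.
- **Participant Retention and Discontinuation Protocols.** When a participant withdraws or deviates, procedures stop, and "the specific outcome data collected and retained for these individuals will consist of baseline serum MDA, T-SOD, and telomerase levels", together with the time of and reason for exit. No post-intervention value is among the data kept.
- **Statistical Handling of Missing Data.** "the incidence of missing data is anticipated to be extremely low (<5" percent. Missing values are assumed MCAR because they would arise strictly from random logistical or laboratory anomalies. Available pairs (pairwise deletion) are primary, and baseline observation carried forward (BOCF) is the sensitivity analysis. The Sensitivity Analyses section says that if significance agrees between the two, the findings count as stable and free of attrition bias.
- **Trial Estimand, Handling of Intercurrent Events.** Dropout, voluntary withdrawal and nonadherence are listed as anticipated. A while-on-treatment strategy is chosen, and missing values after the event are to be handled by multiple imputation so that attrition does not bias the result.

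**The concern.** The protocol supports MCAR with one argument: the cause of every missing value is a random logistical or laboratory fault. The expected rate is offered as further reassurance. Other sections provide for participants who leave or deviate, keep no post value for them, and size the trial with a 20% allowance for dropout. Leaving an emesis or purgation programme is not a laboratory or logistical fault, and it may be related to how the participant tolerates or responds to it.

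What is at stake is the reading of the primary result. If losses are mainly withdrawals, the mean change in available pairs describes those who completed, and the number of pairs may be well below the 53 on which the stated power depends. The estimand section and the missing-data section also name different methods for the same missing values, so the analyst has no single rule to follow.

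**Working it through.** **1. Reproducing the 53.** Inputs from Sample Size: z = 1.96, P = 0.5, d = 0.15, dropout 20%.

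- n = 1.96² × 0.5 × 0.5 / 0.15² = 42.68.
- With 20% loss: 42.68 / 0.80 = 53.4, which is 53 to the nearest whole number.
- With 5% loss: 42.68 / 0.95 = 44.9, that is 45.

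The stated size therefore has the 20% allowance built in.

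**2. Counts, if 53 is the number enrolled.**

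- 20% dropout: 53 × 0.20 = 10.6, so 10 to 11 missing post values and about 42 pairs.
- Under 5%: 53 × 0.05 = 2.65, so at most 2 missing and at least 51 pairs.
- If the true dropout rate were 20%, the binomial chance of 2 or fewer dropouts among 53 would be about 0.0007.

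**3. Power of the two-sided paired t test at d = 0.395 (noncentral t, alpha 0.05).**

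| Complete pairs | Power | d detectable at 80% power |
|---|---|---|
| 53 | 80.6% | 0.392 |
| 51 | 79.0% | 0.400 |
| 42 | 70.5% | 0.443 |

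The stated 80% reproduces, but it needs all 53 pairs. The dropout allowance given in the same section is not deducted.

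**4. Can BOCF detect the problem?** Take 42 pairs with observed mean change 0.395 and SD 1.

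- Available pairs: t = 0.395 × √42 = 2.560 on 41 df, P = 0.0143.
- Add 11 zeros: mean = 0.395 × 42/53 = 0.313. Sum of squares about the new mean = 41 + 42 × 0.395² − 53 × 0.313² = 42.36. SD = √(42.36/52) = 0.903. t = 0.313 / (0.903/√53) = 2.525 on 52 df, P = 0.0147.
- With observed d = 0.32, the P values are 0.0444 and 0.0447.

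The zeros pull the mean towards zero, but they also shrink the SD and raise n, so the P value hardly moves. The two analyses will nearly always agree on significance, whatever caused the losses.

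**5. Possible bias, by assumption only.** Let D be the difference in true mean change between completers and non-completers, in SD units. The completer mean differs from the all-enrolled mean by (missing fraction) × D. The documents give no value for D. For an assumed D of 0.5 to 1, the difference is 0.10 to 0.20 SD at 20% missing and 0.025 to 0.05 SD at 5%.

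**The case against.** Several points on the other side are fair.

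- **An allowance is not a forecast.** Planning for 20% while expecting under 5% is ordinary caution, and inpatient stay with observed dosing gives the low forecast some basis. A reader might infer that the two figures cannot both stand or that the sample size is miscalculated. The documents do not support that: the arithmetic reproduces, and the figures are unreconciled rather than impossible together.
- **The denominator is unclear.** The Expected Completion section ends the trial once 53 volunteers have completed the protocol with both laboratory evaluations. On that reading the under-5% figure could describe laboratory loss among completers, with dropouts outside it. The sizing formula points the other way, since its 53 already includes the dropout allowance. The counts in steps 2 and 3 hold only if 53 is the number enrolled.
- **The declared target is close to completers.** The while-on-treatment strategy aims at the effect while participants adhere, so the all-enrolled mean in step 5 is not the protocol's stated target. This stands, and it is a reason to label the result plainly. It does not make losses random, and the same section asks for multiple imputation.
- **BOCF covers deviations as well as laboratory loss.** It does, and at 20% missing it reduces the mean change to 0.8 of the available-pair value. But the stated criterion compares P values, and step 4 shows that this comparison is uninformative.

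Two further inferences are tempting. One is that most losses will come from people abandoning oleation, emesis or purgation; the protocol gives no expected reasons for dropout. The other is that 0.395 SD is the effect the trial was sized for; the protocol calls the size feasibility-driven and presents 0.395 as a retrospective sensitivity figure.

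**Conclusion.** The concern holds as a conflict between sections. The stated basis for MCAR, and so for pairwise deletion as the primary method, is contradicted by the withdrawals and nonadherence that the protocol itself anticipates and for which it keeps no post value. That conclusion does not depend on what 53 counts: replacing dropouts would restore the number of pairs but would not make the losses random.

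The size does depend on it. If 53 are enrolled and 20% leave, about 42 pairs remain and power at d = 0.395 is about 70.5% rather than the stated 80%. If 53 is the completer count, the power statement stands and the two rates may simply have different denominators, which the text should then say. The bias range rests wholly on an assumed D, and the realised loss rate is unknown. The trial is exploratory, which limits the consequence. Even so, the plan to declare freedom from attrition bias when BOCF agrees would claim more than that check can show.

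**What to change.** - In Sample Size and in Statistical Handling of Missing Data, state one expected loss rate with its denominator (enrolled or completers), separating dropout from laboratory loss. If under 5% is the real expectation for all losses, correct or explain the 20% allowance; if 20% is, carry it into the missing-data section and give the power for the expected number of pairs.
- Delete the statement that omissions come strictly from random causes as the justification for MCAR.
- Name one primary missing-data method and make it agree with the estimand section, which now asks for multiple imputation.
- Label the available-pair result as the mean change in completers.
- In Sensitivity Analyses, remove the conclusion that agreement in significance with BOCF shows freedom from attrition bias.

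The cost is mainly wording, plus a decision on the primary method. The article reports data analysis as pending, so the change can be made before results are seen. The price is a less favourable completeness statement or a smaller dropout allowance.
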